### Data Collection

Data will be collected at three time points–baseline, 4-, and 12-month. Each subject will be asked to attend an in-person assessment appointment at the HF clinic from which he/she is recruited (Toronto, Montreal, or Vancouver) at each time point. During each assessment, subjects will be asked to complete specified physiological tests and self-report questionnaires (on paper or Web-based). There will be two exceptions: (1) subjects will complete the Web-based DHQ II, and (2) wear the accelerometer at home for seven days after their baseline assessment, and immediately prior to their 4- and 12-month assessments.

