#### Secondary Hypotheses

Our secondary hypotheses are that the e-Counseling + Usual Care arm will be associated with significant improvement in the quality of life, adherence to self-care, and psychological adjustment from baseline to 4- and 12-month assessments. These outcomes will be measured using the following objective and validated indices: (1) the KCCQ (≥5 points increase in the summary score at the 4-month assessment) for quality of life, (2) the Canadian version of the Diet History Questionnaire II (DHQ II) [40] for diet habits, (3) the mean 4-day step count (as measured by accelerometry) [41,42] and the Physical Activity Scale for the Elderly (PASE) questionnaire [43] for physical activity level, (4) the medication possession ratio (MPR) [20] for medication adherence, (5) the generalized anxiety disorder (GAD-7) scale [44] and Patient Health Questionnaire (PHQ-9) [45] for anxiety and depressive symptoms, respectively, (6) the Perceived Stress Scale (PSS) [46] for stress level, and (7) Prochaska’s algorithm [47] for readiness to change self-care behaviors.

In addition, we hypothesize that the e-Counseling + usual care group will perform better than the Control groups at the 12-month assessment on the following prognostic measures of cardiovascular functioning: (1) increased exercise capacity as measured by the 6-minute walk test (6MWT) [48], (2) increased vagal-heart rate modulation [44,45] as measured by electrocardiography (ECG), (3) decreased values of the Seattle Heart Failure Model (SHFM) [49-51], N-terminal pro-brain natriuretic peptide (NT-proBNP) [52,53], high sensitivity C-reactive protein (hsCRP) [52,54], and (4) increased VO_2_ peak [55] during cardiopulmonary exercise testing.

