### Recruitment Procedure

Cardiologists, who are coinvestigators in this trial, will identify patients with CHF in their care who meet our recruitment criteria. A clinic staff member will introduce the study to the potential subjects and solicit their verbal consent to be contacted by our research team. The contact information of consented individuals will be sent via secure fax to the Behavioral Cardiology Research Unit at University Health Network (UHN), Toronto, Canada. Individuals will be telephoned by our research team to obtain verbal consent to participate and to schedule a baseline assessment appointment to be held at one of the three trial sites (Toronto, Montreal, and Vancouver). We will obtain written informed consent from subjects for trial participation, email communication, and review of medication history at the beginning of their baseline assessment appointment. Once they have completed their baseline assessment, subjects will be randomized into the intervention or control group. We have received ethics approval from our coordination site (UHN). At the time of manuscript submission, we are seeking ethics approval from the Vancouver and Montreal trial sites.

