#### Secondary Outcomes

The quality of life at the 4-month interval will be assessed by determining the number of subjects who demonstrate a ≥5-point improvement of the KCCQ total score [38,39].

The subjects’ increase in adherence to the recommended intake of vegetables, fruit, dairy, and dietary fat will be evaluated at the 4- and 12-month assessments using the Canadian version [40] of the DHQ II [75], which is also available in French.

The physical activity level of the subjects will be measured in two ways: (1) mean step count, and (2) self-report questionnaire. We will ask subjects to document their daily step count for 7 days prior to their assessments at baseline, 4-, and 12 months. The step count will be measured using an accelerometer (LifeSource/A&D XL-18CN Activity Monitor) that we will provide to each subject. We will calculate the mean 4-day step count using data from the three weekdays and one weekend day that have the highest step count out of the 7-day record [76,77]. Adherence to physical activity over the past week will be measured by the PASE [78], which has been validated in persons with CHF [79]. We will use a French version that was translated by its publisher.

We will confirm the smoking status of those who self-report as a current smoker at the baseline, 4-, and 12-month assessments using salivary cotinine. The current smokers will be defined by having salivary cotinine level ≥10 ng/ml. These subjects will also be screened for the use of nicotine replacement therapy, which can confound their salivary cotinine result. Smoking history will be evaluated using questions from the Survey on Living with Chronic Disease in Canada [80] (ie, “Have you smoked at least 100 cigarettes in your life?”). The French version [80] of the smoking history questions will be also used in this trial.

We will estimate each subject’s medication adherence using MPR [81]. It calculates the cumulative medication supply for *x* days, divided by the total days to the next reﬁll or end of the observation period. MPR has been validated in a previous trial [20]. We will measure MPR with pharmacy refill data for a 4-month period that precedes each of the three assessments.

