#### Statistical Analysis

This trial will use a 2 parallel-group design with 3 repeated assessments at baseline, 4-, and 12-months. A generalized mixed model (GMM) will evaluate the primary outcome, which is a binary code of whether the 12-month KCCQ [39] increases ≥5 points [38]. Predictors will include baseline KCCQ, age, sex, body mass index, and Group (e-Counseling vs Control). The primary outcome will be coded as a “failure” in the event of CHF hospitalization or mortality, but not for “elective” medical procedures (eg, cardiac resynchronization therapy). GMM with repeated measures will assess binary secondary outcomes across 4- and 12-month intervals (eg, KCCQ and smoking status). This analysis is optimal as it adjusts for serial correlations across repeated measures and between individual subjects in each group. Predictors will include baseline KCCQ, age, sex, body mass index, time (4- vs 12- month assessment interval), and Group (e-Counseling vs Control). Significant interactions or main effects will be followed by Bonferroni post hoc tests for significance, *P*<.05, 2-sided. Data missing at random will be handled by multiple imputations. For continuous secondary outcomes, linear mixed models (LMM) [94] for repeated measures with a random intercept will assess whether within-subject improvement across 4- and 12-month intervals is independently associated with our e-Counseling protocol. This analysis adjusts for serial correlations across repeated measures and between subjects in each Group. Predictors will include the baseline dependent variable, age, sex, body mass index, time (4- vs 12-month assessment interval), and Group (e-Counseling vs Control). LMM with a random intercept will also evaluate whether e-Counseling vs Control demonstrates improvement at the 12-month interval in VO_2_ peak, NT-proBNP, hsCRP, and the SHFM.

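### The baseline step-count week is placed before the baseline assessment in one section and after it in another; on the second wording the baseline covariate can be recorded after allocation

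*Protocol article*

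**What the plan says.** Mean step count by accelerometer is a secondary outcome at 4 and 12 months (Secondary Hypotheses). Two sections of the protocol article fix its measurement window.

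- Secondary Outcomes: "We will ask subjects to document their daily step count for 7 days prior to their assessments at baseline, 4-, and 12 months".
- Data Collection: subjects are to "wear the accelerometer at home for seven days after their baseline assessment", and to wear it just before each of the two later assessments.

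The sections agree on the 4- and 12-month windows and disagree on baseline.

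Three other statements matter. Recruitment Procedure says: "Once they have completed their baseline assessment, subjects will be randomized into the intervention or control group". Table 1 gives weekly e-messages in months 1 to 4 (16 messages), out of 28 over the year, and the Control Group section gives the control arm the same schedule. For continuous secondary outcomes, Statistical Analysis says: "Predictors will include the baseline dependent variable, age, sex, body mass index, time" and Group.

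**The concern.** The two windows cannot both be followed, and each raises a difficulty.

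The earlier window is awkward to carry out. The accelerometer is one "that we will provide to each subject", and written consent is taken "at the beginning of their baseline assessment appointment". Verbal consent is obtained by telephone beforehand, so a device could be sent out in advance, but the article does not say that this will happen. Sites may therefore drift to the later window, or differ from one another.

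The later window raises the statistical question. If the assessment ends with the clinic visit and randomisation follows it, the baseline week starts after allocation, and the first weekly message may arrive during it. A covariate measured then can respond to treatment, and adjusting for it removes part of the effect that the model is meant to estimate. A baseline that was recorded after allocation cannot be measured again later, so the point needs settling before enrolment.

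**Working it through.** **1. Order of events under each wording**

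| Step | Secondary Outcomes wording | Data Collection wording |
|---|---|---|
| Seven-day baseline record | before the baseline assessment | after the baseline assessment |
| Written consent | start of baseline appointment, so after the record | start of baseline appointment, so before the record |
| Randomisation | after the assessment, so after the record | after the assessment; may be before or during the record |
| First weekly e-message | after the record | may fall within the record |

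The article gives no interval between the visit, randomisation and the first message.

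**2. Effect on the adjusted estimate**

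Let D be the true between-arm difference in steps at follow-up, b the within-arm slope of follow-up on baseline (equal to the correlation if the standard deviations are equal), and f the fraction of D already present between the arms in the baseline week. Then

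adjusted effect = D - b x (between-arm difference at baseline) = D - b x f x D = D x (1 - b x f).

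The share lost is b x f. A simulation at b = 0.7 and f = 0.25 returned 0.825 x D, matching 1 - 0.7 x 0.25 = 0.825. That value of f was chosen only to test the formula.

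**3. Inputs**

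- b: not in the article. Assumed range 0.5 to 0.7.
- f: not in the article. Seven days of a weekly schedule hold one message, or two if messages fall at both ends. If the effect builds up in proportion to messages received by month 4, f is 1/16 = 6.25% or 2/16 = 12.5%. If no message precedes the end of the record, f is 0.

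**4. Results**

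| f | b = 0.5 | b = 0.7 |
|---|---|---|
| 0 | 0% | 0% |
| 1/16 | 0.5 x 0.0625 = 3.1% | 0.7 x 0.0625 = 4.4% |
| 2/16 | 0.5 x 0.125 = 6.3% | 0.7 x 0.125 = 8.8% |

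Counting against all 28 messages instead, f is 1/28 to 2/28 and the loss is 0.5 x 3.6% = 1.8% to 0.7 x 7.1% = 5.0%.

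**5. What this means for power**

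The article does not power the step count. For an outcome that would otherwise have 80% power at two-sided 0.05, and with the standard error unchanged, power becomes Phi(2.80 x (1 - b x f) - 1.96). At the largest loss, 2.80 x 0.9125 - 1.96 = 0.60, or about 72%. At the smallest non-zero loss, 2.80 x 0.96875 - 1.96 = 0.75, or about 77%.

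The article states no figure that depends on this point, so there is none to reproduce.

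**The case against.** The best answer is that recording after randomisation is inferred and not stated. Recruitment Procedure distinguishes the assessment from the appointment. Data Collection lists the home record as an exception to what is done at the visit, which allows it to be read as a part of the assessment completed at home. On that reading randomisation waits for the record and no bias arises. This stands as a possibility. It is not the plain reading, because Data Collection places the week after the assessment, and it does nothing to remove the contradiction with Secondary Outcomes.

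It also stands that only a difference between arms matters. Both arms wear the device and receive messages on the same schedule, so a shared reaction to the device or to enrolment drops out of the comparison.

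A reader might infer more than the text supports:

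- **A large loss.** Putting f at 20% to 50% gives 0.5 x 20% = 10% up to 0.7 x 50% = 35%. Nothing in the article supports so much of the effect appearing in a week that holds one or two of 16 messages. The Intervention section describes working through readiness and ambivalence before behaviour change, which also points to a slow start.
- **The same contradiction for the Diet History Questionnaire II (DHQ II).** Data Collection mentions the Web-based questionnaire in the same sentence, but the words about seven days after baseline belong to the accelerometer item. No section clearly places the baseline questionnaire after the visit.
- **A threat to the trial's main result.** Step count is one of many secondary outcomes, physical activity is also measured by a self-report scale, and the KCCQ primary outcome does not use this record.

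**Conclusion.** The contradiction is certain: the two sections give opposite windows for the same baseline measurement. That the later window falls after allocation is the plain reading of the sections taken together, but the article does not fix it.

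If it does fall there, the adjusted step-count effect shrinks by about 0% to 9%. That range rests on an assumed slope of 0.5 to 0.7 and on an effect that accrues with messages received. The loss is zero if allocation or the first message waits for the record. A between-arm difference in the same direction as the later effect biases the result toward no effect, so a false claim of benefit is not the main worry. The sample size and the primary analysis are untouched. This is a should-fix point on one secondary outcome.

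**What to change.** Reconcile Secondary Outcomes and Data Collection so that both give one baseline window. State that the seven-day baseline accelerometer record is completed after consent, before allocation is released and before the first e-message. As a precaution, have the baseline Web-based DHQ II completed before allocation too, since its timing is not clearly stated.

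Where a subject's record nevertheless overlaps allocation, flag it and repeat the step-count analysis without using those subjects' baseline record, as a sensitivity analysis. Setting such baselines to missing by rule is not recommended: it replaces an observed value that carries a small possible shift with an imputed one, and nothing shows that to be better.

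The cost is about one week between the baseline visit and randomisation, a check that the home record is complete before allocation is released, and wording changes in the sections named. No new measurement is needed.

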### Subject Compliance Monitoring

As a quality control check, we will evaluate the number of emails sent to subjects versus the number of proactive emails that subjects have opened via automated reply. This will yield a ratio of adherence to treatment (number of emails sent/number of emails opened) that will be considered as a potential covariate in supplemental outcome analyses.

Problems with adherence/compliance to preventive counseling are often due to increased response burden that is disproportionate to perceived benefit [90]. To offset this problem, we will inform subjects that they can keep the accelerometer (approximate value=US $50) as a gesture of appreciation for their participation. Transportation/parking, up to US $21, will also be reimbursed. Finally, we expect to reinforce subject motivation to comply with trial procedures by maintaining a regular schedule of e-messages over 12 months, which are likely to be perceived as being supportive in nature.

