The CHF-CePPORT e-Counseling protocol will be delivered in collaboration with the Consumer eHealth platform of the Heart and Stroke Foundation of Canada. It will send 28 emails proactively to each subject in the intervention arm over a 12-month interval (Table 1). Each email will link e-Counseling subjects to a restricted section of our e-platform where they will access multimedia materials and interactive e-tools. As noted above, the clinical method and content of this protocol is consistent with principles of MI. In keeping with I-START [19,22], the e-Counseling messages promote the following: (1) explicit validation of the subject’s stage of “readiness” for behavior change via e-messaging and educational segments, (2) collaborative participation by means of subject-selected menus and explicit messaging to validate the subject’s active participation, and (3) reinforcement of “change talk” [63] through peer modeling, dramatic vignettes, and self-help exercises that are designed to help resolve ambivalence to change. Additionally, MI is most efficacious when combined with other evidence-based counseling methods such as cognitive-behavioral therapy [66]. Accordingly, the e-Counseling protocol will maintain a user-centered approach by working collaboratively with each subject who reports appropriate motivation to change a behavior that they have identified as a priority for change. This includes interactive access to the following therapeutic tools: (1) self-help information and e-tools for self-monitoring self-care behaviors, and (2) developing cognitive-behavioral skills to build and strengthen efficacy [73] to initiate and maintain behavior change. The collaborative tone of the e-Counseling content is consistent with cognitive-behavioral guidelines to reinforce motivation [59,63] and efficacy [73]. Finally, subject engagement in this segment of the e-Counseling program will be reinforced through the use of short films that will complement the e-based self-help information and e-tools. These original short films have been written and produced by our research team, in collaboration with the Heart and Stroke Foundation of Ontario. e-Counseling subjects will continue to receive CHF-related medical care from their health care team during the course of the trial (ie, usual care).

**Table 1 table1:** The 12-month schedule for proactive e-messaging for the CHF-CePPORT trial.

	Month 1-4	Month 5-8	Month 9-12

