#### Control Group

In addition to usual care, the Control group will be provided with e-messages following the same delivery schedule (Table 1). The e-messages will include brief articles that are randomly selected from the Healthy Living section of the Heart and Stroke Foundation of Canada e-platform. Each e-support article will provide information tailored for a CHF population, such as appointments with physicians and advice about heart healthy guidelines for exercise, diet, smoke-free living, symptom monitoring, and medications. This intervention will be distinct from the e-Counseling group in two ways: (1) information will not be tailored to each subject’s stage of readiness for change, and (2) e-messages will not include e-tools and e-Counseling procedures to increase “readiness” and efficacy to adhere to targeted self-care behaviors.

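### The protocol leaves email opening, a post-randomisation measure that the arm can change, available as a covariate in supplemental outcome analyses; entered beside Group, it can bias the e-Counseling effect in either direction

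*Protocol article*

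**What the plan says.** Subject Compliance Monitoring describes the measure: "we will evaluate the number of emails sent to subjects versus the number of proactive emails that subjects have opened via automated reply". The result is a "ratio of adherence to treatment (number of emails sent/number of emails opened"), and this ratio "will be considered as a potential covariate in supplemental outcome analyses". Nothing there restricts the measure to one arm.

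Both arms generate it. For e-Counseling, "It will send 28 emails proactively to each subject in the intervention arm over a 12-month interval". Under Control Group, "the Control group will be provided with e-messages following the same delivery schedule (Table 1").

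The content differs by design. In the intervention arm, "Each email will link e-Counseling subjects to a restricted section of our e-platform where they will access multimedia materials and interactive e-tools", and "subject engagement in this segment of the e-Counseling program will be reinforced through the use of short films". For Control, "information will not be tailored to each subject’s stage of readiness for change", and the messages carry no e-tools.

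Three other places bear on the point:
- Recruitment Procedure places randomisation after the baseline assessment.
- Statistical Analysis lists the predictors of the primary model as baseline KCCQ, age, sex, body mass index and Group. The repeated-measures models use the baseline value, age, sex, body mass index, time and Group. The email ratio is in neither list.
- Planned Subgroup Analysis uses the same ratio separately, to study dose-response.

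**The concern.** A covariate in a randomised comparison is safe when it is fixed before randomisation. This one builds up over the 12 months that follow, and the two arms receive different material through the emails being counted. Tailored messages, films and interactive tools could raise opening through greater interest or lower it through greater burden.

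Opening is also likely to be tied to outcome. Motivation plausibly drives both. In addition, Statistical Analysis codes CHF hospitalisation or death as failure on the primary outcome. If messages continue to be sent during such an event, fewer will be opened, and the outcome then alters the covariate.

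Two things go wrong if the ratio sits beside Group. Any benefit that works through engagement is adjusted away, and e-Counseling openers are compared with a differently selected set of control openers. The result would invite the reading that it is the effect of e-Counseling at equal adherence. Under these conditions it is neither that nor the effect of the randomised programme.

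**Working it through.** The protocol gives no figure for this point, so there is nothing to reproduce. It also gives no opening rates and no link between opening and outcome, so every simulation input below is an assumption except the 28 emails. Effects are in percentage points of responders, not KCCQ points.

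**Step 1: why the coefficient moves.** In a linear model,

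adjusted Group effect = unadjusted Group effect − γ × Δ,

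where Δ is mean opening in e-Counseling minus mean opening in Control, and γ is the slope of outcome on opening with Group in the model. Adjustment changes nothing if Δ = 0 or γ = 0. Otherwise the direction of the change depends on the signs of both.

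**Step 2: linear illustration.** 400,000 subjects per scenario, U an unmeasured standard normal trait, 28 emails each.
- Log-odds of opening = 0.4 + a·Group + U, with a = 0, 0.8 or −0.8. U is left out of this formula in the last row below.
- Response probability = 0.40 + true direct effect·Group + b·U + d·(opened share − 0.6).
- b = 0.1 when openers have the better prognosis and −0.1 when they have the worse. d = 0.5 only where opening itself acts, and there b = 0.

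| True direct effect | Opening, Control / e-Counseling | Link of opening to outcome | Unadjusted | Adjusted |
|---|---|---|---|---|
| 0 | 58.2% / 58.2% | openers do better | 0.0 | 0.0 |
| 0 | 58.3% / 73.1% | openers do better | −0.1 | −6.7 |
| 0 | 58.2% / 41.8% | openers do better | −0.1 | +6.7 |
| 0 | 58.2% / 73.1% | openers do worse | +0.2 | +6.7 |
| 20 | 58.2% / 73.2% | openers do better | 19.9 | 13.3 |
| 20 | 58.2% / 41.8% | openers do better | 20.1 | 27.0 |
| 10 | 58.2% / 73.2% | opening itself acts | 17.3 | 9.9 |
| 10 | 59.9% / 76.9% | none | 9.9 | 9.8 |

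The formula in step 1 accounts for these rows. In row 2, Δ = 73.1 − 58.3 = 14.8 points and the shift is −6.7 − (−0.1) = −6.6, so γ = 6.6/14.8 = 0.45. In row 3, Δ = 41.8 − 58.2 = −16.4 and the shift is +6.8, so γ = 6.8/16.4 = 0.41.

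In row 7 the total effect should be 10 + 0.5 × (73.2 − 58.2) = 17.5, close to the simulated 17.3. Adjustment leaves only the direct 10.

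Rows 1 and 8 are the two cases without bias: equal opening, and opening unrelated to outcome.

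**Step 3: logistic illustration.** 200,000 subjects per scenario.
- Log-odds of opening = 0.2 + 0.8U + a·Group, with a = 0.5, −0.5 or 1.0.
- Log-odds of response = −0.75 + 0.6U + b·Group, with b = 0 for no effect and b = 0.9 for about 20 points.
- Control opens 54%.

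Where repeated runs differed, the range is shown.

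| e-Counseling opening | Adjusted effect, truth 0 | Adjusted effect, truth about 20 |
|---|---|---|
| 65% | −6 (OR 0.75) | 13 to 14 |
| 43% | +6.2 to +6.5 (OR 1.35 to 1.36) | 26 to 27 |
| 74% | −11.5 to −12 | 7 |

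**Step 4: scale.** Sample Size Estimation plans on 53% against 33%, which is 53 − 33 = 20 points. An error of 6 to 7 points is about a third of that (6.7/20 = 0.34).

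**The case against.** The strongest reply is that the sentence commits to very little. It names no model and no Group term, calls the covariate only potential, and confines it to supplemental work. The dose-response analysis under Planned Subgroup Analysis may be the very analysis meant, and there the ratio is the exposure of interest and not an adjustment. This stands in part, because the protocol does not say that the ratio will be entered beside Group. But it describes the covariate use and the dose-response use in separate sections, and an outcome analysis with a covariate naturally includes an arm comparison. The wording permits the problem and nothing excludes it.

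A second reply is that the main analysis already limits its covariates properly. That is correct. A reader might infer that the trial's e-Counseling effect is itself biased. The documents do not support this: the ratio is absent from the predictors listed under Statistical Analysis, and the Abstract puts the primary outcome on an intention-to-treat basis.

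A third reply is that bias is possible but not shown. This also stands. The schedule is identical, subjects are said to be blinded, and no opening rates are given. Differing content makes an arm effect on opening plausible, not established.

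Finally, the magnitudes do not measure the planned covariate. They use opened/sent, whereas the protocol writes sent/opened, which is a nonlinear inverse and undefined when nothing is opened. They also leave out baseline KCCQ, age, sex and body mass index, which could absorb some of the prognostic difference. So they show that the error can be material and can go either way, but not how large it would be in this trial.

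**Conclusion.** The point holds as a conditional one. As worded, the plan allows a post-randomisation measure, taken in both arms and open to influence by the arm, to adjust a supplemental arm comparison. The adjusted effect can then be wrong in either direction if the arm affects opening and opening is related to outcome. Under the assumed inputs the error at a true null is about 6 to 7 percentage points for differences in opening of roughly 11 to 16 points, and larger if the arms diverge further.

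Its weight is modest. No primary or secondary model and no design figure changes. What is at risk is a supplemental estimate that could be misread as the effect at equal adherence, and the documents carry no warning against that reading.

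**What to change.** In Subject Compliance Monitoring, replace the sentence on covariate use with a statement that the email ratio will not be a covariate in any model that estimates the Group effect, and that email opening will be reported descriptively by arm. State that covariates in arm comparisons, supplemental ones included, are limited to values fixed before randomisation.

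Label any adherence-related analysis, including dose-response, as exploratory and non-randomised. An instrumental-variable or complier analysis with randomisation as the instrument is optional. It should be done only if use of the e-Counseling material is actually measured, since the protocol describes recording email opening but not use of the e-tools or the restricted section. It must also state its exclusion assumption, namely that assignment affects outcome only through the level of use specified.

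The cost is a sentence or two of wording and the loss of an adherence-adjusted arm comparison. The required changes need no new data and no change to the sample size or primary analysis.
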